| Definition of the Study population This study will examine two patient cohorts who are at risk of CKD, diabetic and hypertensive patients. Eligible patients must have information recorded at least 12 months prior to the study index date and have up to standard (UTS). The study population will include patient records from January 2005 to January 2019.  **Inclusion criteria**  Cohort 1 (CH1) will include type 2 diabetes mellitus (T2D) patients along with any one of the following criteria (see Appendix 1 for the inclusion exclusion flow chart):   - Newly diagnosed T2D (MEDCODE 758 : Type 2 diabetes mellitus) - 2 prescriptions of diabetic medication (See Appendix 3 for the list of all drugs) - Hemoglobin A1c (HbA1c) value greater than 6.5   Cohort 2 (CH2) will include essential hypertension (EHT) patients along with the following criteria (see Appendix 2 for the inclusion exclusion flow chart):   - Newly diagnosed essential hypertension (see Appendix 4 for list of Read codes)   Time related variable including the index date and the follow-up is described in the following figure:  **Rolling index date**  (The date first diagnosed with DM2 or HT**)**  Pre-index period  1 years  Acute disease period  2 years  Follow up period  (Median follow up 5 years, minimum follow up 1 year)  **End of follow up**  (Either the date patient has transferred out from the practice  Or the last date of the record in the dataset)  **CH1**: no DM2 diagnosis nor related medication during this period **CH2**: no HT diagnosis nor DM2 diagnosis nor related medication during this period  Baseline is characterized based on the observation in these periods  January 2005  January 2019  **Exclusion criteria**  We will exclude the following patients based on the Read code during acute disease period (2 years after the rolling index date):   - Liver dysfunction including drug induced liver injury (diagnosis with Read code listed in Appendix 5 and/or Aspartate transaminase (AST) and alanine transaminase (ALT) levels outside of the normal range (AST: 8-48U/L, ALT: 7-55U/L) - Anemia (hemoglobin level below cutoff, female:120 male:130 g/L, or with the clinical annotation of primary or secondary anemia with the Read code listed in Appendix 6) - Human immunodeficiency virus (HIV) infection and or on HIV related medications (see Appendix 7). - All malignancies and or on medications related to the treatment for the malignancies (see Appendix 8). - Age < 40 (to exclude type 1 diabetic patients). - Any user of UGT1a1 inhibitors (see Appendix 9) during the acute disease period. - < 1 year of clinical records in the database before the index date - Pregnant women - Patients with clinical record of alcohol dependencies. - Any patients with less than two bilirubin measurements during the acute disease period.   **Objective-specific exclusion criteria**  For each endpoint, we impose the following additional exclusion criterion:   - For objectives 1a) and 1b) with the endpoint “First two consecutive measurements of eGFR that are 30 percent less than the last eGFR record during the acute disease period”, we will exclude patients without eGFR records during the acute disease period (2 years after the rolling index date). - For objectives 2a) and 2b) with the endpoint “First observation of albuminuria (UACR >30mg/g) during the follow up period.”, we will exclude patients with recorded UACR more than 30mg/g during the acute disease period. - For objectives 3a) and 3b) with the endpoint “First observation of proteinuria during the follow up period, we will exclude the patients with the recorded proteinuria (protein dipstick test result +, ++, or +++) during the acute disease period. |

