| Selection of comparison group(s) or controls We will stratify the patients based on the population median of the patient mean baseline serum bilirubin levels from the tests table under ENTTYPE 158. We consider the patients with less than or equal to the median serum bilirubin level to be the control group, and patients with greater than the median serum bilirubin level to be the exposure group.  The serum bilirubin levels are determined by the average of all the available measurements during the acute disease period (2 years after the rolling index date). We require at least two bilirubin measurements to be used to obtain an average estimate (this will account for the variability of bilirubin measurements). |
| Exposures, Outcomes and Covariates **Outcome:**  Outcomes will include the following events:  Primary objective: eGFR decline  1) First two consecutive measurements of eGFR that are 30 percent less than the last eGFR record during the acute disease period.  eGFR will be calculated using CKD EPI formula based on the recorded serum creatinine measurements in tests table ENTTYPE 165.  Secondary objective: Proteinuria  2) First observation of the proteinuria  Proteinuria is defined as the protein dipstick test results either +, ++ or +++, recorded in the tests table under ENTTYPE 431.  Exploratory objective: Albuminuria  3) First observation of the albuminuria  Albuminuria is defined as the recorded UACR measure in test table under ENTTYPE 469 greater than 30mg/g.  **Covariates:**  We will use all the available covariates (see Appendix 10) to calculate the propensity score that we will use for the inverse probability weighting of the Cox proportional hazard model.  We will include all the available covariates (see Appendix 10) in the baseline table.  We will include the following selected covariates in the multivariate Cox proportional hazard model:   - Age, Sex, Weight, BMI, Baseline eGFR, Baseline UACR, Baseline protein dipstick result, Smoking status, Serum Haemoglobin level, HDL cholesterol, LDL cholesterol - Use of the following drugs: ACE inhibitor, Statin, Diuretics, Opioids, Potassium-sparing diuretics |

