| Patient or user group involvement (if applicable) No patient/user groups will be engaged in any way.  This is an explorative study to better understand the impact of bilirubin on a population level. Furthermore, no patients will be contacted we will only use CPRD retrospective data and we do not have any plans to assess quality of life. This is an exploratory study which will further our scientific knowledge about the impact of bilirubin on renal outcomes and potentially support the design of future clinical trials. |
| Plans for disseminating and communicating study results, including the presence or absence of any restrictions on the extent and timing of publication We plan to communicate the study result regardless of either positive or negative result though academic publication in a medical journal. As this is an academic project for the postdoctoral research fellow (YA) and he is hired for this project with time limiting contract (ending September 2020, extendable up to September 2021) hence the manuscript needs to be submitted to the journal before the end of his contract.  **Conflict of interest statement:**  All the investigators are employed by AstraZeneca, however, this study does not focus on AstraZeneca or any other medicines. |
| Limitations of the study design, data sources, and analytic methods As bilirubin is endogenous substance, the patients are exposed to them throughout their entire life hence the development of type 2 diabetes or hypertension can be affected by bilirubin.  Also, it is known that the natural level of bilirubin depends on the race, gender and other patient characteristics. Hence there will be a bias in baseline characteristics for exposure groups. Furthermore, as our primary analysis compares bilirubin levels it is only possible to conduct these analyses among subjects with bilirubin measurements and baseline measurements of each outcome. This may impact generalizability of the results. Sensitivity analyses will be conducted to address this limitation.  CPRD is a UK database limiting generalizability to other countries. In addition, it may not be possible to rule out the impact of unmeasured confounding factors on the primary/secondary objectives although we will adjust for all the measured confounding factors through the inverse probability weighting. |

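### Follow-up runs on whether or not the renal outcome is tested, so an unexplained difference in testing between bilirubin groups biases the hazard ratio, in a direction the protocol does not reveal

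*Protocol*

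**What the plan says.** In the time-line under Definition of the Study population, follow-up ends at one of two dates: "Either the date patient has transferred out from the practice" "Or the last date of the record in the dataset". Its length is given as "Median follow up 5 years, minimum follow up 1 year". Neither end date depends on a renal test.

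The primary event is "First two consecutive measurements of eGFR that are 30 percent less than the last eGFR record during the acute disease period", so it needs two recorded values after baseline. Albuminuria needs one recorded UACR above the threshold, and proteinuria one positive dipstick. (I name these two by test, because the protocol ranks them differently in different sections.)

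The objective-specific exclusions look only at the two-year acute disease period:

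- eGFR: "we will exclude patients without eGFR records during the acute disease period".
- UACR: "we will exclude patients with recorded UACR more than 30mg/g during the acute disease period".
- Dipstick: "we will exclude the patients with the recorded proteinuria" in that period.

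The last two remove only patients with a recorded positive, so a patient never tested stays in. The Limitations section reads differently: "it is only possible to conduct these analyses among subjects with bilirubin measurements and baseline measurements of each outcome". For UACR and dipstick this does not match the exclusion criteria.

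**The concern.** All three outcomes come from routine-care tests. A patient with fewer than two follow-up creatinine values cannot have the primary event. One with no follow-up UACR or dipstick cannot have the corresponding event. All of them still add event-free time up to the end of the record.

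This does little harm if both bilirubin groups are tested alike. If they are not, the group tested less shows fewer events over the same person-time, and the Cox model reads that as a lower hazard.

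The cohorts are large enough for a small artefact to be statistically significant. The hazard ratio is also the study's main result, and the February 2021 amendment builds a further objective on how it differs between the two cohorts.

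**Working it through.** **1. The plan's own figures.** Inputs from Sample size considerations: HR 0.8, 5% type I error (two-sided reproduces the figure), 80% power. I take the median split as 1:1.

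- Schoenfeld: 4 × (1.960 + 0.842)² / (ln 0.8)² = 630.5, so 631 events, as stated.
- 631 / 0.047 per year = 13 426 person-years, against 13 500 stated.
- At the expected 300 000 person-years: 300 000 × 0.047 = 14 100 events. The HR detectable with 80% power is exp(−2 × 2.802 / √14 100) = 0.954.

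An artefact of about 5% would therefore be detected as an effect.

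**2. What the documents show about testing.** The only objective-specific exclusion for the primary analysis is having no eGFR in the acute disease period, so Feasibility counts gives the share without one:

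- Diabetic cohort: 68 217 − 66 509 = 1 708 (2.5%).
- Hypertensive cohort: 85 409 − 81 025 = 4 384 (5.1%).

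These patients all had at least two bilirubin tests in the same two years. The counts are not split by bilirubin group, and no follow-up testing rate is given.

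**3. Simulation with no true effect.** From the protocol: onset rate 0.047 per year, follow-up of minimum 1 and median 5 years. Assumed: 1:1 groups, follow-up capped at 11 years, all testing rates, and test timing unrelated to renal status. There were 400 000 patients per scenario and an unweighted Cox model, with standard errors of about 0.007 to 0.009. The hazard ratio is high v low bilirubin, with the end of follow-up as written.

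| Assumed testing, high v low bilirubin | One-test outcome | Two-test outcome |
|---|---|---|
| Equal, 1 per year | 0.99 | 1.00 |
| Equal, 30% never tested in both | 0.99 | 1.00 |
| Never tested 20% v 10% | 0.88 | 0.88 |
| Never tested 10% v 20% | 1.15 | 1.14 |
| 0.8 v 1.0 tests per year | 0.95 | 0.91 |
| 1.0 v 0.8 tests per year | 1.04 | 1.10 |
| 0.5 v 1.0 tests per year | 0.83 | 0.68 |

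Ending time at risk at the last informative test, among patients with enough follow-up tests, gives 0.99 to 1.02 in every scenario.

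Masking is equally possible. With a true HR of 0.80 and 10% v 20% never tested, the rule as written gives 0.93 (one test) and 0.92 (two tests).

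**4. Testing that rises with illness.** Person-time rate ratios, true ratio 1.0, follow-up uniform over 1 to 9 years, same onset rate. Rates are low v high bilirubin:

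- A: two-test outcome, 2.0 v 1.6 tests per year.
- B: two-test outcome, 1.5 v 1.2 per year, 5% v 10% never tested.
- C: one-test outcome, 0.5 v 0.4 per year, 30% v 40% never tested.

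| Testing after onset | End of follow-up | A | B | C |
|---|---|---|---|---|
| Unchanged | As written | 0.95 | 0.86 | 0.79 |
| Unchanged | Last informative test | 1.00 | 0.98 | 1.02 |
| Tripled | As written | 0.99 | 0.92 | 0.80 |
| Tripled | Last informative test | 1.04 | 1.05 | 1.03 |

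When illness prompts testing, the bias under the written rule is smaller and last-test censoring overshoots.

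**The case against.** **The plan already handles part of this.** Baseline eGFR, UACR and dipstick result are model covariates, and missing values get an indicator, so whether a patient was tested at baseline is largely adjusted for. Age, BMI, smoking and drug use also enter, and the weights use all listed covariates. This stands for the part of a testing difference that baseline covariates explain. It does not reach differences arising in follow-up, because the weights model bilirubin group and not outcome testing.

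**The primary outcome is better protected.** A baseline eGFR is required, at least two bilirubin tests select patients under regular blood testing, and the planned mixed model on eGFR uses observed values only. This stands, and it makes 10% or 20% never tested look high for eGFR. The mixed model does not correct the hazard ratio, however, and there is no counterpart for UACR or dipstick.

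**Censoring detail may be in an analysis plan not shown.** It may be, but the protocol itself fixes the end of follow-up and the exclusions. Its one check on selection by measurement compares patients with and without a baseline bilirubin test.

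**A stronger reading is tempting.** The amendment reports hazard ratios of 0.82 to 0.91, and a reader might infer that differential testing produced them. The documents do not support that. They give no testing rates by bilirubin group, freely chosen rates can reproduce almost any ratio, and the reported values come from the study's analyses while the simulation is unadjusted.

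**Conclusion.** The concern holds with neutral direction. Untested time counts as event-free, and nothing in the protocol measures or corrects this for the hazard ratio. The apparent ratio under no true effect ranges from about 0.68 to 1.15 across the assumed testing differences, and is 0.99 to 1.00 when testing is equal, even with 30% never tested in both groups.

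That range rests on assumed rates and an unadjusted model, so it shows what the rule permits and is not an estimate of the bias in this study. The protocol does not support a claim that the bias favours the hypothesis. The exposure is likely smaller for eGFR than for UACR and dipstick. Should-fix.

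**What to change.** - For each objective and cohort, tabulate by bilirubin group the outcome tests per person-year and the share of patients with too few follow-up tests to have the event (two for eGFR, one for UACR or dipstick).
- Pre-specify a sensitivity analysis among patients with enough follow-up tests that ends time at risk at the last informative test: the last-but-one eGFR, or the last UACR or dipstick. An interval-censored model is an alternative.
- Report it beside the current analysis, not in place of it, and qualify the conclusion if the hazard ratio shifts materially.
- Reconcile the Limitations statement on baseline outcome measurements with the exclusion criteria for UACR and dipstick.

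The cost is some programming on data already held. The sensitivity analysis loses some patients and person-time, but the margin is wide: 13 500 person-years needed against over 300 000 expected. Last-test censoring can itself be biased if testing rises with illness (about 1.03 to 1.05 above), which is why it should not become the primary analysis.

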| Objectives, Specific Aims and Rationale Overall Primary Objective:  1a) To investigate the risk of worsening of renal function using eGFR (using CKD EPI formula) in relation to bilirubin levels in type2 diabetic patients, in a real-world setting.  1b) To investigate the risk of worsening of renal function using eGFR in relation to bilirubin levels in hypertensive patients, in a real-world setting.  Secondary objectives:  2a) To investigate the risk of worsening of renal function using urine albumin creatinine ratio (UACR) in relation to bilirubin levels in type2 diabetic patients, in a real-world setting.  2b) To investigate the risk of worsening of renal function using UACR in relation to bilirubin levels in hypertensive patients, in a real-world setting.  Exploratory objectives:  3a) To investigate the risk of worsening of renal function using amount of protein in urine in relation to bilirubin levels in type2 diabetic patients, in a real-world setting.  3b) To investigate the risk of worsening of renal function using amount of protein in urine in relation to bilirubin levels in hypertensive patients, in a real-world setting.  Specific aims:   \| **Primary objectives**  1a) To investigate the risk of worsening of renal function using eGFR in relation to bilirubin levels in type2 diabetic patients, in a real-world setting.  1b) To investigate the risk of worsening of renal function using eGFR in relation to bilirubin levels in hypertensive patients, in a real-world setting. \| **Outcome measure**  Time to first of first two consecutive measurements of eGFR that are 30 percent less than the eGFR at baseline. \| **Hypothesis tested**  1a) Naturally elevated serum bilirubin level of type2 diabetic patients is associated with slower degradation of the renal function when renal function is measured using eGFR.  1b) Naturally elevated serum bilirubin level of hypertensive patients is associated with slower degradation of the renal function when renal function is measured using eGFR. \| \| --- \| --- \| --- \| \| **Secondary objective**  2a) To investigate the risk of worsening of renal function using urine UACR in relation to bilirubin levels in type2 diabetic patients, in a real-world setting.  2b) To investigate the risk of worsening of renal function using UACR in relation to bilirubin levels in hypertensive patients, in a real-world setting. \| **Outcome measure**  Time to first observation of albuminuria (UACR >30mg/g) during the follow up period. \| **Hypothesis tested**  2a) Naturally elevated serum bilirubin level of type2 diabetic patients is associated with slower degradation of the renal function when renal function evaluated by UACR.  2b) Naturally elevated serum bilirubin level of hypertensive patients is associated with slower degradation of the renal function when renal function evaluated by UACR. \| \| **Exploratory objective**  3a) To investigate the risk of worsening of renal function using amount of protein in urine in relation to bilirubin levels in type2 diabetic patients, in a real-world setting.  3b) To investigate the risk of worsening of renal function using amount of protein in urine in relation to bilirubin levels in hypertensive patients, in a real-world setting. \| **Outcome measure**  Time to first observation of proteinuria during the follow up period. \| **Hypothesis tested**  3a) Naturally elevated serum bilirubin level of type2 diabetic patients is associated with slower degradation of the renal function when renal function evaluated by proteinuria.  3b) Naturally elevated serum bilirubin level of hypertensive patients is associated with slower degradation of the renal function when renal function evaluated by proteinuria. \|   **Rational:**  Recent investigations as well as meta-analyses indicate a strong association between serum bilirubin concentrations and renal outcomes. This association has led us to hypothesis that elevated bilirubin level is associated with slower degradation of kidney function. There are still discussions on this association because the previous investigations lack diversity in the patient population and did not adjust for the key confounders. We wish to conduct a retrospective study in a real-world setting to support or dispute this hypothesis. This study will provide the medical community extra piece of evidence for or against the bilirubin as a potential predictive marker for CKD progression as well as the target for preventative treatment option. |

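### The Read-code exclusions search only the two years after the index date, so liver disease or alcohol dependence coded only earlier can remain in a study of naturally elevated bilirubin

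*Protocol*

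**What the plan says.** Protocol, Definition of the Study population, Exclusion criteria: the lead-in reads "We will exclude the following patients based on the Read code during acute disease period (2 years after the rolling index date". The bullets relevant here are:

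- Liver dysfunction: "diagnosis with Read code listed in Appendix 5 and/or Aspartate transaminase (AST) and alanine transaminase (ALT) levels outside of the normal range".
- Alcohol: "Patients with clinical record of alcohol dependencies", with no window of its own.
- UGT1A1 inhibitors: "Any user of UGT1a1 inhibitors (see Appendix 9) during the acute disease period", which states its window again.
- Record length: "< 1 year of clinical records in the database before the index date", which cannot follow a window that starts at index.

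The same section requires at least 12 months of records before index and uses that year to rule out earlier diabetes or hypertension. The text of the timing figure adds: "Baseline is characterized based on the observation in these periods".

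Under Selection of comparison group(s) or controls, bilirubin is averaged over the two years after index and split at the population median, with no upper limit. The hypotheses under Objectives, Specific Aims and Rationale all take the form "Naturally elevated serum bilirubin level of type2 diabetic patients is associated with slower degradation of the renal function", with a matching version for hypertension.

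**The concern.** Excluding liver dysfunction, anaemia and UGT1A1-inhibitor use helps bilirubin differences reflect natural variation rather than disease or drugs. A chronic liver or alcohol diagnosis does not lapse at the index date, and a practice may code it once and not again. A code search that starts at index misses such a patient even when the diagnosis lies in the pre-index year that every patient must have.

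If these patients have bilirubin raised by disease, some are counted as exposed when their bilirubin is not naturally elevated. If their renal prognosis is also worse, they raise the event rate in the exposed group and hide part of any protective association. This concerns validity, not power, and a large sample does not reduce it.

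**Working it through.** **1. Who can remain under the literal text**

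| Condition coded only before index | Still caught in the acute period by | Not caught |
|---|---|---|
| Liver disease | a new code, or AST/ALT out of range | not re-coded, and enzymes in range or unmeasured |
| Alcohol dependence | a new code | not re-coded, if the lead-in governs this bullet |

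For alcohol the text is also unclear. The record-length bullet cannot obey the lead-in, and the UGT1A1 and bilirubin-count bullets repeat the window as if the lead-in did not settle it. The alcohol bullet could therefore mean any record at any time.

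**2. Whether the analysis repairs it**

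The covariates listed for the multivariate Cox model include neither liver disease nor alcohol. No planned sensitivity analysis varies the exclusion window. The propensity score uses Appendix 10, whose content is not in the text at hand.

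**3. The plan's own figures**

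Inputs from Sample size considerations: hazard ratio 0.8, 5% type I error (two-sided reproduces the figure), 80% power. The median split gives equal groups.

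- Events (Schoenfeld) = (1.960 + 0.842)² / (0.25 × (ln 0.8)²) = 630.5, so 631, as stated.
- Person-years = 631 / 0.047 = 13 426, against the stated 13 500.
- Expected events = 300 000 × 0.047 = 14 100.
- SE of log HR = 2 / √14 100 = 0.0168.

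None of these depends on the exclusion window.

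**4. Illustration of size (f and k are assumptions)**

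Let f be the excess share of the above-median group with such disease, and k its renal hazard relative to the low group. As a simple approximation, mixed HR = (1 − f) × 0.88 + f × k. The shift in SE is ln(mixed / 0.88) / 0.0168. The 0.88 is the diabetic-cohort result for the primary endpoint quoted in the February 2021 amendment.

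| f | k | Mixed HR | Shift in SE |
|---|---|---|---|
| 0.5% | 1.5 | 0.995 × 0.88 + 0.0075 = 0.883 | 0.21 |
| 1% | 2 | 0.99 × 0.88 + 0.02 = 0.891 | 0.75 |
| 2% | 2 | 0.98 × 0.88 + 0.04 = 0.902 | 1.49 |
| 2% | 3 | 0.98 × 0.88 + 0.06 = 0.922 | 2.79 |

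The 0.88 is an observed value, so it would already contain any such bias. Turning the formula round, HR without these patients = (0.88 − f × k) / (1 − f). The same four rows give 0.877, 0.869, 0.857 and 0.837.

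Starting from the planning value of 0.8 instead, f = 1% and k = 2 gives 0.99 × 0.8 + 0.02 = 0.812.

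**5. What it would take to reach 1**

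f = (1 − 0.88) / (k − 0.88). With k = 2 this is 0.12 / 1.12 = 10.7%. With k = 3 it is 0.12 / 2.12 = 5.7%. Both are well above the assumed range.

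**The case against.** The strongest reply is that the gap is narrow and its effect unproven. Patients who are re-coded or have enzymes out of range in the window are excluded. Exposure is a median split, not a pathological threshold, and nothing in the documents shows that patients with old, un-recoded disease and normal enzymes fall above the median. If they are spread evenly, f is 0 and the formula gives no shift. The flow charts in Appendices 1 and 2 and the covariates in Appendix 10 are not in the text at hand and might add a search or an adjustment. The planned alternative cut-offs and continuous bilirubin analysis could reveal a different risk at high values, and the limitations section admits unmeasured confounding.

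Most of this stands as a limit on size and certainty. It does not supply the missing search: alternative cut-offs leave the patients in, and if an appendix looks further back, the lead-in conflicts with it and needs correcting.

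A reader might infer more than the text supports:

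- That all patients with earlier disease stay in. The criteria in the acute period remove many of them.
- That HIV is an equal gap. HIV medication in the window also excludes, and the documents give no link between HIV itself and bilirubin.
- That the hazard ratio could pass 1. The worst scenario above is 0.922.
- That the reported protective association is an artefact of this gap. Under the stated assumptions the bias runs towards 1, so it would weaken such an association, not create it.

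**Conclusion.** The point holds in a limited form. As written, the code search omits the pre-index year, so patients with liver disease or alcohol dependence coded only before index, and not caught again afterwards, can remain. That sits badly with hypotheses about naturally elevated bilirubin. For alcohol dependence the defect is at least an unclear window.

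The size cannot be derived from the documents. For f of 0.5% to 2% and k of 1.5 to 3, a hazard ratio of 0.88 moves to between 0.883 and 0.922, or 0.2 to 2.8 standard errors. This rests on assumed f and k, on these patients being over-represented above the median, on a simple mixture formula, and on an event rate carried over from a randomised trial. The amendment's primary-endpoint results, 0.88 and 0.91, are close enough to 1 for a modest shift to matter in interpretation.

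**What to change.** In Definition of the Study population:

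- State the search window for each exclusion separately.
- Apply the code exclusions for liver disease (Appendix 5) and alcohol dependence to the mandatory pre-index year plus the acute disease period.
- Leave the laboratory and UGT1A1-inhibitor windows as they are.
- Re-run the feasibility counts, and report by cohort and bilirubin group how many patients are coded only before index.

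Because results already exist, the minimum is a sensitivity analysis, labelled as added afterwards, that repeats the primary and secondary analyses without these patients. A search of all earlier records is useful as a further check but not as the main rule, because its length varies with time registered at the practice. The pre-index year is guaranteed for everyone.

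The cost is a short protocol change, a re-run of the cohort code and a slightly smaller cohort. The margin is ample, with 13 500 person-years needed against about 300 000 expected. No new data are required.
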